### Procedure

The study timeline is shown in Table 1. Boys who have consumed any alcohol within the last 12 months before initial assessment and who and their parents/caregivers have given written informed consent will be included in the study (t_0_ timing of enrolment). They undergo the baseline measures about the length of two sessions (t_1_ and t_2_). In case they do not fulfill the inclusion criteria of alcohol use they will be invited to be part of the non-intervention registry. In case they fulfill all inclusion criteria participants will be randomised to either the intervention group or control group in a 1:1 allocation ratio. A central randomisation list will be created with variable block lengths stratified by the recruitment locations school vs. clinics, outpatient clinics and practices. Enrolled participants will be randomized on the base of computer-generated random numbers provided by a research associate of the Institute of Medical Biometry and Epidemiology (IMBE) of the University Medical Center Hamburg-Eppendorf. This assistant is not involved in the practical implementation of the research project. After randomisation, participants get the training over six sessions. After completion of the treatment, participants take part in the post-measurements (t_3_-t_4_). During the post-measurement, the app (movisensXS) is installed on the smartphone of the participants. In case of compatibility problems, a smartphone is handed out to the test persons by the study staff. This smartphone will be only usable for the follow-up survey. For 12 months after intervention, every Sunday afternoon, participants get an app-based reminder and are asked to join the short follow-up survey. Here, they retrospectively report on their substance consumption for the last week directly on their smartphones (t_5_-t_57_) by answering questions via the app.

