### Statistical analysis

#### Sample size

For the primary outcome “time to first event of drunkenness”, we calculated the sample size for a logrank test comparing the intervention and control group. In the literature, we did not find data referring to students with MBID for precise estimating of the base rates of survival. Hence, we refer to the European School Survey Project on Alcohol and other Drugs (ESPAD, see Introduction). ESPAD-data indicates that about 60% of students report at least one event of drunkenness during the last year, which makes an event-free survival rate of 0.4 in the control group. In the absence of evidence-based assumptions on the effectiveness of the intervention, we estimate that the intervention will drop down the events of drunkenness from a base rate of 60 to 28%, which corresponds to an event-free survival rate of 0.72 in the intervention group. This leads to a hazard ratio of 0.36. With a power of 80% and a significance level of 5% (two-sided hypothesis), we need an overall sample size of 82 participants (41 participants per group) to detect this difference. We assume that we lose 30% of the participants in each group during the study duration. These observations are censored. Furthermore, we expect no one to switch groups. The study is planned without accrual period.

For the most important secondary outcomes “quantity of alcohol units /number of tobacco cigarettes”, we can show median effects of .65 in terms of Cohens d with this sample size and with a type I error of α = .05 (two-sided hypothesis), a power of 1-β = .80 and a correlation between baseline and follow-up of r = .50. The sample size calculation was conducted with PASS 15 based on the modules “Logrank Tests” and “Analysis of Covariance”.

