#### Statistical methods for primary and secondary outcomes

The descriptive statistics will be presented separately for every group and for the total sample. The primary and secondary analysis will be based on the intention-to-treat population, which includes all participants randomised. For the primary outcome “time to first event of drunkenness”, a logrank test will be calculated to compare group differences in survival curves. The resulting statistical test for group comparison will be performed two-sided at the 5% significance level. The analysis will be repeated in the per-protocol population. In an additional analysis, we will extend this time-to-event-analysis to a Cox regression to adjust our results for the following covariates: intelligence, age, mindfulness, mental health, and family risks. If the event “drunkenness” occurs frequently enough in the individual participant, for the secondary analysis we will use an appropriate extension of the Cox model to deal with recurrent events and a Poisson regression using the count of the events as the dependent variable. For the most important secondary outcomes, change from baseline of the number of alcohol units and change from baseline of the number of cigarettes, a baseline-adjusted linear mixed model will be calculated for each outcome with participants as a random effect and group (intervention vs. control), time and recruitment location (schools vs. clinics, outpatient clinics, and practices) as fixed effects, and the respective baseline value as a covariate. The time by group interaction will be tested, and if the interaction is not significant, the interaction will not be included in the model. In this model, missing values will be directly imputed to enable an intention-to-treat analysis, which results in unbiased estimators under the missing-at-random-assumption. For further secondary outcomes (neuropsychological testing and questionnaires), a baseline adjusted analysis of covariance will be determined with the respective change from baseline to post-intervention as a dependent variable, group and recruitment location as independent variables, and the respective baseline value as a covariate. The analysis of all secondary outcomes will be performed in an exploratory manner. Interim analyses are not planned. Exploratory analyses will be performed for possible intervening factors, such as neurobehavioural parameters, mindfulness (trait) or quality of life. The analysis of the registry study will be performed in an exploratory manner. Probabilities of starting to consume alcohol will be described descriptively.

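### Randomisation is stratified by recruitment location, but the primary logrank test and the other drunkenness-event analyses do not name it; stratifying the test is a nearly free improvement

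*Protocol article*

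**What the plan says.** Under Procedure, boys are "randomised to either the intervention group or control group in a 1:1 allocation ratio", and the list is stratified: "A central randomisation list will be created with variable block lengths stratified by the recruitment locations school vs. clinics, outpatient clinics and practices". This is the only stratification factor named.

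Under Statistical methods for primary and secondary outcomes, the models are given outcome by outcome:

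- Primary outcome, time to first drunkenness: "a logrank test will be calculated to compare group differences in survival curves". No strata are named.
- Additional Cox regression, "to adjust our results for the following covariates: intelligence, age, mindfulness, mental health, and family risks". Location is not on this list.
- Recurrent-event extension of the Cox model and Poisson regression on event counts: no location term is named.
- Linear mixed models for alcohol units and cigarettes: location is included, with "recruitment location (schools vs. clinics, outpatient clinics, and practices) as fixed effects".
- ANCOVAs for the tests and questionnaires: location is included, with "group and recruitment location as independent variables".

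The Sample size section plans a two-group logrank test with 82 boys, 80% power and a two-sided 5% level.

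**The concern.** The design factor is carried into the change-from-baseline models, which the article calls exploratory, and into none of the analyses of drunkenness events. The one confirmatory test is among those left out. Because the article spells out model terms for each outcome, an analysis plan that followed it literally would repeat the mismatch.

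Stratified randomisation forces the arms to be similar on location. If location also predicts the outcome, the arms differ by chance less than the plain logrank variance assumes. The test then rejects less often than 5% under the null and detects a true effect less often than a test that uses the strata. About 31 events are expected and the power is planned at 80%, so there is little slack.

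A prognostic effect of location is plausible from the text. Recruitment includes psychiatric units, and the Background treats behavioural and emotional problems as assumed predictors of substance use. The age range is 11 to 17 in clinical recruitment and 13 to 17 in schools. Lifetime drinking in the cited German school survey rises from 8.7% at age 11 to 72.4% at age 15. None of this gives a drunkenness rate by location.

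**Working it through.** **Step 1: the plan's own figure.** Inputs from Sample size: 12-month event-free survival 0.40 and 0.72, 30% loss per group treated as censored, no accrual period, two-sided 5%, 80% power.

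- Hazard ratio: ln 0.72 / ln 0.40 = 0.3285 / 0.9163 = 0.3585, which agrees with the stated 0.36.
- Events (Schoenfeld): 4 × (1.960 + 0.842)² / (ln 0.3585)² = 31.40 / 1.052 = 29.8, so 30.
- With exponential loss (rate −ln 0.70 = 0.3567), the probability of an observed event is h/(h+c) × (1 − e^−(h+c)). Control: 0.9163/1.2730 × (1 − e^−1.2730) = 0.518. Intervention: 0.3285/0.6852 × (1 − e^−0.6852) = 0.238. Mean: 0.378.
- N = 30 / 0.378 = 79.4, so 80. At N=82, 82 × 0.378 = 31 events are expected and power is 81.5%.
- A Lakatos-type calculation with the same loss gives N = 84.5 and power 78.8% at 82.

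The stated 82 is therefore reproduced to within a few participants, and it refers to a plain two-group test.

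**Step 2: plain against stratified logrank at N=82.** There were 8,000 simulated trials per scenario, with two locations, permuted blocks within location, 30% exponential loss, overall control survival fixed at 0.40, and a treatment hazard ratio of 0.3585 within each location (1 for type I error).

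These inputs are not in the documents and are assumed: block sizes of 2, 4 and 6; exponential times without weekly ties; a higher-risk location holding 20%, 30% or 50% of boys; and the location hazard ratio. Ranges below run over the three shares.

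| Location HR | Type I error, plain | Type I error, stratified | Power, plain | Power, stratified | Gain from stratifying (points) |
|---|---|---|---|---|---|
| 1 | 5.0–5.2% | 5.0% | 80% | 79–80% | −0.4 to −0.2 |
| 1.5 | 4.5–4.8% | 4.5–5.1% | 78–80% | 79% | −0.2 to 0.5 |
| 2 | 4.1–4.4% | 4.8–5.2% | 78–79% | 79–80% | 0.8 to 1.6 |
| 3 | 3.7–4.0% | 5.2–5.6% | 76–77% | 80–81% | 3.5 to 4.4 |
| 5 | 2.2–3.2% | 5.1–5.3% | 69–71% | 81–82% | 9.5 to 12.4 |

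The Monte Carlo standard error is about 0.25 points for type I error and 0.45 for power. The highest stratified type I error, 5.6%, is one of 15 scenarios and lies about two standard errors above 5%.

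**Step 3: what the power column means.** The simulation takes 0.3585 as the hazard ratio within each location. With a strong location effect the overall intervention survival is then below 0.72. Example: 30% of boys at higher risk and a location HR of 5. The low-risk control hazard a solves 0.7e^−a + 0.3e^−5a = 0.40, so a = 0.598. Intervention survival is 0.7e^−0.214 + 0.3e^−1.072 = 0.565 + 0.103 = 0.668. Part of the fall of the plain test below 80% therefore reflects a weaker overall contrast than the plan assumed. The result to rely on is the gap between the two tests under the same truth, not the absolute fall.

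**The case against.** The strongest reply is that the unstratified test is valid and matches the sample size calculation. Type I error stays at or below about 5%, and power is about 80% when location does not matter. That stands: there is no false-positive risk, and the planned N is not wrong.

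Second, a large location effect is not established. Every randomised boy has drunk alcohol in the past year, and alcohol or drug dependence and severe psychiatric disorders requiring on-site treatment are excluded in both settings. The wider age range adds only 11- and 12-year-olds to the clinical group, which would tend to lower its risk, while psychiatric burden would tend to raise it. The two could partly cancel. The age gradient in the Background concerns lifetime drinking in general school samples, not drunkenness among boys who already drink. This stands too, and it makes the size of the loss conditional.

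Third, the Cox model already adjusts for age and mental health, the likely channels of a location effect. That helps the additional analysis but does nothing for the primary test.

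Fourth, an article may leave strata to the analysis plan. As a general rule that is fair. Here, though, the same section names location for some models and omits it from others, including a listed covariate set, so this is more than brevity.

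A reader might infer that every secondary model contains location and the primary test alone lacks it. That is not so: the recurrent-event and Poisson models name no location term. A reader might also infer that location was chosen because it is known to be prognostic. The article gives no reason for the choice.

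**Conclusion.** The mismatch is real: location governs the randomisation and enters the mixed models and ANCOVAs, but is not named for the primary logrank test, the Cox extension, or the recurrent-event and Poisson models. The consequence is conditional. If location is prognostic, the plain test is conservative and gives up power relative to a stratified one: negligible at an assumed location hazard ratio of 1.5, about 1 to 2 points at 2, 3 to 4 at 3, and 9 to 12 at 5. If location is not prognostic, stratifying costs at most about 1 point (0.2 to 0.4 in the simulation).

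It is tempting to say flatly that the planned test is conservative and wastes power. The documents do not support that, because they report neither drunkenness by location nor the expected school/clinic split. The figures also assume exponential times, exponential loss and the same treatment hazard ratio in both locations. The point is a free improvement, not a defect that invalidates the analysis.

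**What to change.** Before any outcome data are seen, state that the primary analysis is a two-sided logrank test stratified by recruitment location, using the same two categories as the randomisation list. Stratify the Cox model by that factor, or add it as a covariate to the existing list, and do the same for the recurrent-event model; add location as a covariate to the Poisson regression. Keep the unstratified logrank test as a named sensitivity analysis.

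The choice has to be fixed in advance, since picking between the two tests after seeing results would be data-driven. The change takes a sentence or two, needs no new data and leaves N at 82. Its price is at most about 1 point of power if location turns out not to matter.

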#### Inclusion and exclusion criteria

Boys will be included in the randomised trial if
they and their parents/cargegivers give informed consentthey have declared that they have drunk alcohol during the past yearthey are between 11 and 17 years (clinical/institution recruitment) or between 13 and 17 years (school recruitment)they are diagnosed with having a MBID (70 < I.Q. < 85) or if they are educated in a school for learning disability

The decision about fulfilling the inclusion criteria, and therefore randomisation, can be made only after informed consent was given. This is due to the fact, that many boys have problems to admit, that they drank alcohol, when their parents are around. A clear picture on their consumption pattern will be gained only in the more intimate situation of the first measurement (t_1_). Interested boys who meet the criteria but who had not drank alcohol in the previous year are directed to the registry (see Fig. 1) and receive neither the intervention nor the control intervention. Based on estimations from the feasibility study, we plan an oversampling of at least *n* = 38 persons.

Boys will be excluded from randomisation if they have 1) no experiences of drinking in the last year; 2) display severe psychiatric disorders requiring on-site treatment or dependence on alcohol or drugs; 3) have a cognitive impairment with I.Q. ≤ 70. In case they fulfill the second or third criteria, boys will be excluded completely from the study. Boys only fulfilling the first criterion will be directed into the registry and will be observed for a possible initiation of drinking during the study period of 1 year.

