##### Substance use

The Timeline Followback (TLFB) is a calendar method in which participants are asked retrospectively about their consumption of alcohol, nicotine, cannabis and other drugs, establishing a 30-days-before baseline and a post-measurement calendar [49].

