##### Intelligence

The Wechsler Nonverbal Scale of Ability (WNV) is a non-verbal general cognitive ability assessment for children, teenagers, and young adults aged 4 to 21. The brief version lasts requires 15–20 min and consists of the two subtests matrices and spatial span [53]. It will be used in cases when no sufficient information about intelligence level or schooling can be found.

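### The supportive adjusted Cox model leaves out baseline drinking and the randomisation stratum, and includes intelligence, which the trial does not measure systematically

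*Protocol article*

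**What the plan says.** All places are in the Protocol article.

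- **Primary test** (Statistical methods for primary and secondary outcomes): "a logrank test will be calculated to compare group differences in survival curves".
- **Adjusted model** (same section): "In an additional analysis, we will extend this time-to-event-analysis to a Cox regression", in order "to adjust our results for the following covariates: intelligence, age, mindfulness, mental health, and family risks". Neither baseline drinking nor recruitment location is named.
- **Linear models** (same section): the mixed model for alcohol units and cigarettes has "time and recruitment location (schools vs. clinics, outpatient clinics, and practices) as fixed effects", with the baseline value as covariate. The analysis of covariance for the further secondary outcomes also uses location and the baseline value.
- **Randomisation** (Procedure): the list is "stratified by the recruitment locations school vs. clinics, outpatient clinics and practices".
- **Baseline drinking** (Substance use, under Pre/post measurements): the TLFB covers alcohol, nicotine, cannabis and other drugs, "establishing a 30-days-before baseline and a post-measurement calendar".
- **Entry** (Inclusion and exclusion criteria): a boy qualifies on an IQ between 70 and 85 "or if they are educated in a school for learning disability". An IQ of 70 or below excludes.
- **Intelligence test** (Intelligence): "It will be used in cases when no sufficient information about intelligence level or schooling can be found".

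**The concern.** Any drinking in the past year is enough for entry, so baseline exposure may range from a single occasion to frequent drinking. Recent drinking is a natural candidate predictor of time to the next drunkenness. The protocol itself says in its Background that early use predicts later use, and its sample size section assumes a correlation of 0.50 between baseline and follow-up for the quantity outcomes. Leaving it out means that a chance imbalance between arms of 41 goes uncorrected in the one time-to-event model meant to adjust for imbalance, and possible precision is lost.

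The stratum is a matter of consistency. Location stratifies the allocation and enters every linear model, but not the Cox model.

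Intelligence raises the reverse problem. It is listed, yet the trial's own test is given only where information on intelligence level or schooling is lacking. A boy admitted on schooling need not be tested. If scores are missing and the software drops those boys, the adjusted result no longer covers everyone randomised.

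**Working it through.** **1. Reproduce the plan's figure.** Inputs from Sample size: event-free survival 0.40 (control) and 0.72 (intervention), 80% power, two-sided 5%, 30% loss treated as censoring, no accrual period, 41 per arm.

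- Hazard ratio = ln(0.72)/ln(0.40) = 0.3285/0.9163 = 0.3585, as stated (0.36).
- Events (Schoenfeld) = 4 × (1.960 + 0.842)² / ln(0.3585)² = 29.8, so 30.
- Yearly hazards are 0.9163 and 0.3285; the loss hazard is −ln(0.70) = 0.3567.
- Event probability, control: 0.9163/1.2730 × (1 − 0.40 × 0.70) = 0.518.
- Event probability, intervention: 0.3285/0.6852 × (1 − 0.72 × 0.70) = 0.238.
- Mean probability 0.378, so N = 29.8/0.378 = 78.9, i.e. 80 in equal arms, against 82 stated. At N = 82, expected events = 41 × (0.518 + 0.238) = 31.0, with power 0.815.

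The planned size is reproduced closely.

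**2. Events per parameter** (each covariate as one term).

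- Planned: treatment + 5 covariates, 31/6 = 5.2.
- Baseline drinking and location both added as terms: 31/8 = 3.9.
- Drinking added, location as a stratum: 31/7 = 4.4.
- Drinking in place of intelligence, location as a stratum: 31/6 = 5.2.

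**3. Power of the Cox model.** Simulated trials of 82 boys with 30% loss, calibrated so that arm-level survival is 0.40 and 0.72. The five planned covariates are taken as non-prognostic. The strength of baseline drinking is assumed, because the documents give none.

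| Log HR per SD of baseline drinking (assumed) | Unadjusted Cox | Planned five | Planned five + drinking + location | Difference, last two columns (points) |
|---|---|---|---|---|
| 0 | 0.784 | 0.772 | 0.776 | 0.4 |
| 0.4 | 0.793 | 0.781 | 0.814 | 3.3 |
| 0.7 | 0.799 | 0.793 | 0.861 | 6.8 |
| 1.0 | 0.809 | 0.798 | 0.919 | 12.1 |

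Replacing intelligence by drinking, with location as a term, gave 0.807–0.814 at 0.4 and 0.848–0.868 at 0.7. A model with only treatment, drinking and location gave 0.878 at 0.7, a gain of 8.5 points over the planned five. With 1,500 to 2,000 runs per setting, the simulation error of each power is about √(0.8 × 0.2/1,500) = 0.010 or less. Roughly 3 to 8 points is therefore a fair summary for 0.4 to 0.7.

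**4. If boys without an IQ score were dropped.** The missing share is assumed.

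| IQ missing | Boys left | Events (× 0.378) | Simulated power, planned model |
|---|---|---|---|
| 10% | 82 × 0.9 = 74 | 28 | 0.73–0.74 |
| 30% | 82 × 0.7 = 57 | 22 | 0.61–0.64 |
| 50% | 82 × 0.5 = 41 | 16 | 0.46–0.47 |

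This table shows what is at stake under complete-case fitting. It is not a forecast.

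**The case against.** The strongest reply is that the Cox model is only an additional analysis. The logrank test is primary, the sample size was calculated for it, and no confirmatory decision rests on the Cox result. That stands and limits the weight of the point.

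Four stronger readings are tempting, and the documents do not support them.

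- **School-recruited boys will be lost.** A reader might infer this from the testing rule. But that rule limits only the trial's own test; some boys may have a score on record, and the exclusion at IQ 70 or below presupposes some knowledge of IQ. The article does not say that the Cox model uses complete cases. It bases the primary and secondary analyses on everyone randomised, and handling of missing covariates may properly sit in an analysis plan.
- **A larger power loss.** Taking 0.36 as the hazard ratio conditional on baseline drinking gives 68% unadjusted against 77% adjusted at an SD of 0.7 in log hazard, and 63% against 81% at 1.0. But the plan derives 0.36 from arm-level survivals, so it is a marginal effect, and the smaller figures under working apply.
- **Too many covariates for the events.** In these simulations the five non-prognostic covariates cost about 1 point against the unadjusted model (for example 0.784 to 0.772), and at most about 2 in the further runs (0.803 to 0.779). About 5 events per parameter is thin, but no material power loss was shown.
- **The listed covariates are weak and should go.** The Background gives a reason for each of the disputed ones: degree of cognitive impairment, emotional and behavioural problems, parental drinking, trait mindfulness. A school/clinic indicator does not stand in for IQ. Removing them wholesale would be preference.

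A further limit is that TLFB is a self-reported 30-day window, whereas entry looks back a year. A noisy measure puts the trial towards the lower end of the assumed range.

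**Conclusion.** The point holds as an inconsistency in a supportive analysis. The adjusted Cox model omits a plausible predictor that is already collected and the factor that stratified randomisation, while the linear models in the same paragraph use both the baseline value and location. The primary logrank test and N = 82 stand.

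The size is modest and conditional: about 3 to 8 power points for a log hazard ratio per SD of 0.4 to 0.7, about 12 at 1.0, and none if baseline drinking is not prognostic. These figures rest on the stated survivals and loss, on an assumed prognostic strength, and on treating the other covariates as non-prognostic. No separate gain is claimed for location; the case for it is agreement with the design.

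On intelligence, the supported statement is that the trial does not measure it systematically. Whether anyone would be dropped depends on the share of boys without a score and on how missing covariates are handled, neither of which the article gives.

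**What to change.** Before unblinded analysis, amend the one sentence that lists the Cox covariates:

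1. Add baseline TLFB alcohol use, for example log(1 + units) over the 30 days before baseline.
2. Stratify the Cox model by recruitment location, or include location as a term.
3. Keep intelligence in the main adjusted model only if a score is available for essentially all boys. Otherwise move it to a sensitivity analysis, so that no randomised boy is dropped.

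**Cost.** Wording only, as the added variables are already collected. Adding both terms to the full list leaves about 4 events per parameter; replacing intelligence and using location as a stratum keeps it at about 5. Adjusting for a prognostic covariate also changes what the hazard ratio means. With the marginal value at 0.36, the conditional value in the simulations is 0.34, 0.31 and 0.27 at strengths 0.4, 0.7 and 1.0, so the unadjusted and adjusted ratios should be reported side by side and labelled.

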**Methods:**

In this randomised controlled proof of concept study, 82 boys with MBID who consumed any alcohol during the last year will be randomised either to the 6 week mindfulness oriented intervention or the control group receiving a control intervention equal in dose and length. The intervention group undergoes mindfulness training combined with interactive drug education, while the control group completes a health training combined with the same education. In the intention-to-treat analysis the primary outcome is the self-reported delay of first post-intervention drunkeness within a 12 months follow-up time span, measured weekly with a short app-based questionnaire. Secondary outcome is the use of alcohol, tobacco and other drugs within 30 days post-intervention. Changes in neurobiological behavioural parameters, such as impulse control, reward anticipation, and decision making, are also investigated. Other secondary outcomes regard trait mindfulness, emotion regulation, psychopathological symptoms, peer networks, perceived stress, and quality of life. In addition, a prospective registry will be established to record specific data on the population of 11–17 year old boys with MBID without any alcohol experience.

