#### Secondary and other outcomes

Secondary outcomes include self-reported alcohol use during the first year after intervention as a quantitative measure of consumption taken on a weekly basis using a smartphone-based research tool.

For all participants, the number of cigarettes will be inquired weekly.

Furthermore, emotion regulation, neurobehavioural self-regulation, trait mindfulness, psychological attributes, perceived stress and health-related quality of life and will be measured before and after the intervention. In case of drunkenness events, the weekday of the event and event-related social networks will be recorded. The consumption of illicit drugs of any kind will be asked for on a weekly basis. Sociodemographic data on the adolescent’s family contain consumption habits in the parental household (specific target variables and measurements are listed in Table 1).

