### Plans for data collection

#### Follow up

##### Substance use

Our sampling method via movisensXS involves asking participants weekly about drunkenness events and the consumption of alcohol, tobacco and illicit drugs. For binging events, they will be asked for the timing, quantity and experience. The questioning takes a maximum of 3 min. It starts the first week after the intervention and should be carried out weekly for a total of 52 weeks.

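### A significance test decides whether the time-by-group interaction stays in the mixed model for alcohol units and cigarettes, and no group contrast is named for the case where it stays

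*Protocol article*

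**What the plan says.** In the protocol article, Statistical methods for primary and secondary outcomes, the two leading secondary outcomes are "change from baseline of the number of alcohol units and change from baseline of the number of cigarettes". Each is analysed by a linear mixed model "with participants as a random effect and group (intervention vs. control), time and recruitment location" as fixed effects, with the baseline value as covariate. The rule for the interaction is: "The time by group interaction will be tested, and if the interaction is not significant, the interaction will not be included in the model".

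The section does not say how time is coded (linear or categorical). It names no random effect other than participant and no residual correlation. It gives no group contrast to report when the interaction is retained. It does state that all secondary outcomes are analysed in an exploratory manner.

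On the data, Secondary and other outcomes describes "self-reported alcohol use during the first year after intervention as a quantitative measure of consumption taken on a weekly basis". The follow-up text on substance use says of the app survey: "It starts the first week after the intervention and should be carried out weekly for a total of 52 weeks". The Sample size section gives a detectable effect for these outcomes "with a type I error of α = .05 (two-sided hypothesis"), and no separate level for the interaction test.

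**The concern.** Two things come together.

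**The reported effect is not fixed.** If the interaction is dropped, the group coefficient estimates one difference common to all weeks. If it is kept, what that coefficient means depends on how time is coded, and the plan does not say which contrast then answers the hypothesis of a stronger decrease in consumption. A test on the same data chooses between the branches, and an interval computed afterwards takes no account of that choice. This holds even if the test is perfectly calibrated.

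**The test may not be well calibrated.** A random intercept alone makes weeks 1 and 2 as strongly correlated as weeks 1 and 52. If a boy's consumption in one week carries over to the next, or if boys drift apart over the year, the model-based standard error of a time trend is too small and the interaction is declared significant too often.

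At stake are a possible false statement that the effect changes over time, and a treatment effect for alcohol and cigarettes whose definition is settled only after the data are seen.

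**Working it through.** **1. The plan's own figure.** The Sample size section gives d = 0.65 with 80% power, two-sided 5% and baseline to follow-up correlation r = 0.50, from an analysis-of-covariance module. With n per arm, the test has noncentrality d/√(1−r²) × √(n/2) on 2n−3 degrees of freedom.
- n = 29 (41 × 0.7 = 28.7, rounded): d = 0.649, which matches 0.65.
- n = 41: d = 0.542.

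The figure is reproduced after the planned 30% loss. It describes a single group contrast. The plan yields such a contrast without ambiguity only when the interaction test happens to be non-significant.

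**2. What the two branches estimate.** As an illustration, let the true group difference grow in a straight line from 0 at week 1 to D at week 52.
- Interaction dropped: the group coefficient targets the average over weeks, (0 + D)/2 = D/2.
- Interaction kept, linear time counted from week 1: the group coefficient targets the week 1 difference, 0.
- Interaction kept, time centred at mid-year: it targets D/2.

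The same data could thus be reported as D/2 or 0, depending on the test and on a coding choice that is not stated.

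**3. Error rate of the interaction test, linear time.** Inputs from the document: 41 per arm, 52 weeks, participant as the only named random effect. Assumed: nominal two-sided 5% for the interaction test, Gaussian values, AR(1) residual correlation ρ, and participant variance equal to residual variance.

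Over a long series, the true variance of a within-person slope exceeds the independence value by about (1+ρ)/(1−ρ). The actual error rate is then about 2 × [1 − Φ(1.96/√ratio)].
- ρ = 0.2: ratio 1.2/0.8 = 1.50; 1.96/1.225 = 1.60; error 11%.
- ρ = 0.3: ratio 1.3/0.7 = 1.86; 1.96/1.363 = 1.44; error 15%.
- ρ = 0.5: ratio 1.5/0.5 = 3.00; 1.96/1.732 = 1.13; error 26%.

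Simulation under no group effect (3000 replicates, complete data), rejection rates:

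| ρ | Interaction, linear time | Interaction, categorical time (51 df) | Week-averaged group effect |
|---|---|---|---|
| 0 | 0.044 | 0.053 | 0.048 |
| 0.2 | 0.096 | 0.059 | 0.055 |
| 0.3 | 0.143 | 0.072 | 0.043 |
| 0.5 | 0.253 | 0.091 | 0.051 |

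The simulation error is about √(0.05 × 0.95/3000) = 0.004 at the nominal level.

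**4. Diverging personal trends instead of serial correlation.** Residuals are independent, and the slope SD over the year is in units of the total SD (intercept plus residual).
- Slope SD 0.2 / 0.3 / 0.5: linear time 0.092 / 0.151 / 0.268; categorical time 0.046 / 0.045 / 0.063.

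**5. With dropout.** Fitted mixed models with linear time and 30% dropout (200 replicates each) gave 0.05, 0.155 and 0.185 at ρ = 0, 0.3 and 0.5. The inflation does not depend on complete data.

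**6. Does the remedy work?** Comparing each boy's own slope between groups, which on complete data is equivalent to adding a random slope, gave 0.042 to 0.056 in every scenario.

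**The case against.** The strongest case on the other side is that the inflation is read into silence. Naming participant as a random effect does not exclude a random slope, correlated residuals or robust standard errors, and a condensed article may leave these, and the coding of time, to an analysis plan that is not shown. The document gives no serial correlation or slope variance. With categorical time the excess is modest, and under diverging trends nearly absent. The simulated values are Gaussian, whereas units and cigarettes are counts. This all stands, and it makes the error-rate part conditional.

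The model section also does not say that all 52 weekly values enter, and the abstract describes the outcome differently: "Secondary outcome is the use of alcohol, tobacco and other drugs within 30 days post-intervention". That too stands. The weekly reading rests on the outcome and follow-up sections and on the presence of time as a fixed effect.

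A reader might infer that the interaction test is badly inflated as planned, that a retained interaction necessarily makes the group coefficient a time-zero difference, or that the treatment comparison itself is anti-conservative. The documents support none of these. The first needs assumptions they do not supply. The second holds for uncentred linear time with reference coding, but not for centred time or marginal means. The third is contradicted by the check, where the week-averaged effect stayed near 5%.

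The objection does not remove the keep-or-drop rule. It is stated outright, and a fuller covariance specification would repair the test without fixing the contrast.

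**Conclusion.** The point holds in two parts of unequal strength.

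Firm: the article makes the reported group effect for alcohol units and cigarettes depend on a significance test, with no contrast named for one of the two outcomes of that test. No assumption about correlation is needed.

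Conditional: if the model has only a participant random intercept over 52 weekly values, and lag-1 correlation is 0.2 to 0.5, the deciding test has a type I error of about 10 to 25% with linear time and 6 to 10% with categorical time. It is about 5% if weeks are independent given the intercept. The correlations, the equal variance split and normality are assumptions.

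The consequence is limited. The averaged group comparison keeps its error rate, the secondary outcomes are declared exploratory, and the primary logrank analysis is untouched. The exploratory label does not, however, tell a reader which effect will be reported. The change is worth making because it is cheap, not because the trial's main conclusion is at risk.

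**What to change.** 1. Delete the rule that removes the interaction when it is not significant.
2. Prespecify the group difference averaged over the follow-up weeks as the contrast to be reported for each of the two outcomes, whatever the interaction test shows, and state how time is coded.
3. Report the time-by-group interaction descriptively, with a random slope for time, serially correlated residuals, or robust standard errors clustered by participant.

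This changes analysis wording only, with no added data or participants. The downside is somewhat wider intervals for the time-by-group effect.
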